#### Perceived patient-centred care (patient–professional interaction)

Perceived patient-centred care will be assessed via the 16-item Patient-Professional Interaction Questionnaire (PPIQ).^46^ The PPIQ examines patient-centred care by healthcare professional from the perspective of the patient by evaluating different aspects of the integration between the healthcare professional and the patient. This measure consists of four factors (each comprised of four items), which represents the care they received during the course of the remote monitoring intervention: effective communication (eg, ‘he/she provided me with clear information’), interest in the patient’s agenda (eg, ‘he/she was interested in what I want from care’), empathy (eg, ‘he/she understood my emotions’) and patient involvement in care (eg, ‘he/she gave me time to ask and to talk about the illness’. All items will be scored using a five-point Likert scale (‘not at all’=1, ‘very much’=5). Higher scores are indicative of better patient-centred care. The psychometric attributes of this measure have previously been supported.^46^ Additionally, participants will have the option to provide any further information about their care through an open-ended question.

#### Patient experience interview

Semistructured interviews will be conducted with patients who have undergone remote monitoring as part of their treatment for COVID-19 (n ≈ 20, or until saturation is reached). These interviews will be conducted by trained interviewers. A topic guide has been designed to explore the patient’s experience of the remote monitoring intervention, including their: experience of having COVID-19; interactions with staff during the intervention; experience of the remote mentoring equipment; opinion on remote monitoring compared with treatment-as-usual and opinions on using remote monitoring for other types of conditions. The interviews will take approximately 20 min. Interviews will be conducted via telephone on loudspeaker and recorded using audio-recorder or via video call on Zoom and the video call recorded to facilitate COVID-19 restrictions.

### Data analysis: work package 1

The first objective will be attained using a mixed methods design. First, descriptive statistics will assess the overall patient self-reported patient–professional interaction, adherence to the use of the remote monitoring equipment and acceptance towards the remote monitoring technology and provide the sample characteristics.

Second, structural equation modelling will be used to examine different aspects of user acceptance towards remote monitoring technology, such as the performance expectancy of the equipment from the perspective of the patient. Structural equation modelling is advantageous as it can parse out measurement error, thereby yielding more accurate parameter estimates^47^ and can be applied to medical research.^48 49^ We will also determine the effect of several exogenous covariates such as demographics, pre-existing comorbidities, prior experience with mobile phone applications and patient–professional interaction in predicting user acceptance towards the use of remote monitoring technology. Given the larger sample size required for structural equation modelling, in the event that an insufficient sample size is gathered, then a multiple regression analysis will be conducted instead.

Third, latent classes, or symptom profiles, of COVID-19 and postacute COVID-19 will be examined through latent class analysis (LCA), using robust maximum likelihood estimation. To determine the optimal number of latent classes, models with one to six classes will be examined. To avoid solutions based on local maxima, 500 random sets of starting values will be used followed by 100 final stage optimisations. Several fit indices will be used to determine the fit of each latent class model, including the Akaike information criterion (AIC),^50^ the Bayesian information criterion (BIC),^51^ the sample size-adjusted BIC (ssaBIC),^52^ entropy values and the Lo-Mendell-Rubin-adjusted likelihood ratio test (LMR-A).^53^ Lower AIC, BIC and ssaBIC values and higher entropy values are indicative of better model fit. A non-significant LMR-A value suggests that the model with one less class should be accepted. In the event that an insufficient sample size is gathered, then a cluster analysis will be conducted instead.

Next, to determine the predictors of each symptom profile, a multinomial logistic regression will be performed by regressing the latent classes (identified during the class enumeration process) onto several covariates, using the R3STEP function in Mplus.^54 55^ This three-step procedure involves first identifying the most appropriate latent classes; then obtaining the most likely class memberships based on the posterior probabilities of the LCA, while accounting for the classification uncertainty rate (ie, measurement error) and, finally, the most likely class memberships are analysed with the covariates, thereby accounting for at least some of the misclassification errors.^55 56^

Fourth, the interviews will be transcribed verbatim. A thematic analysis will be conducted using NVivo V.12^57^ to identify common themes throughout the interviews. An inductive approach will be taken to draw out themes, without a pre-existing theory in the literature or based on the researchers’ preconceptions, by one researcher through familiarisation with the data, initial coding, refinement and subsequently grouped into themes to best represent the data. It will then be reviewed by the research team to ensure that all emerging topics are included and consensus is reached. A secondary researcher will independently code a subset of transcripts to assess the internal reliability.

### Measures: work package 2

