One important aspect to consider is the experience of the technology from the patient’s perspective. Patient experience of the intervention is an important aspect in predicting treatment adherence.^29^ One such means of modelling patient experience and adherence in remote monitoring-based interventions is through the technology acceptance model (TAM).^30^ The TAM posits that the use of technology, such as remote monitoring, is the result of one’s behavioural intention to use the technology. Behaviour intention, in turn, can be explained through one’s perceived ease-of-use, perceived usefulness and attitude towards the technology. Alternative models of user acceptance (eg, the theory of planned behaviour (TPB), the unified theory of acceptance and use of technology (UTAUT) and the task-technology fit (TTF) models^31–33^) similarly posit that the use of the technology is the result of one’s behavioural intention to use the technology. However, in predicting behavioural intention, these models also incorporate factors such as subjective norms/social influences that may play an important role in user acceptance.^31^ These models aid in explaining user acceptance by providing a framework to incorporate psychosocial and behaviour theories such as the TPB^34^ and the UTAUT^35^ and have been applied to remote monitoring interventions across varying patient groups.^36–39^

Although research on remote monitoring for COVID-19 symptoms is scant, users of remote monitoring technologies for COVID-19 symptoms have generally reported high satisfaction and ease-of-use across interventions.^16 17^ Moreover, findings suggest that patient’s use of telemedicine systems can be effectively modelled within the TAM and TPB framework.^13 40 41^ As such, these frameworks may be extended to modelling adherence in remote monitoring for patients with COVID-19.

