#### User acceptance of remote monitoring equipment

Patients who report using either a pulse oximeter and a remote monitoring phone application, or just the remote monitoring phone application will be asked to complete a 16-item questionnaire pertaining to their experience of the technology. This multidimensional measure is comprised of items relating to the different factors of user technology acceptance, based on a recent integrated model consisting of factors from the UTAUT and TTF models^33^. Several factors will be extracted from this model, consisting of ‘social influence’ (two items; the degree to which important others agree to the use of the technology; for example, ‘people who influence my behaviour thought it was important that I use the remote monitoring equipment’), ‘facilitating conditions’ (three items; individual’s perception of the availability of resources to use the technology; for example, ‘I felt I had the necessary knowledge to use the remote monitoring equipment’), ‘effort expectancy’ (four items; ease-of-use related to using the technology; for example, ‘I find it easy to use such equipment’), ‘performance expectancy’ (four items; effectiveness to users in performing specific tasks; for example, ‘I feel remote monitoring equipment is useful in obtaining health information’) and ‘TTF’ (three items; the degree to which users believe that the performance of the technology matches its intended use; for example, ‘In general, the remote monitoring equipment fully met my needs’). All items will be rated using a five-point Likert scale (‘strongly disagree’=1, ‘strongly agree’=5), with higher scores reflecting greater scores towards its respective factor. Previous psychometric research has supported the validity and reliability of these items.^33^ Participants will also have the opportunity to share any additional information about their experience through an open-ended question.

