#### Adherence to the use of remote monitoring equipment

Adherence to the use of the pulse oximeter throughout the intervention will be assessed via three statements with participants being asked to choose the statement that best reflects their experience (‘I did not use the oximeter’, ‘I tried to use the oximeter but gave up because it was too difficult’, ‘I occasionally used the oximeter during my treatment’ and ‘I used the oximeter consistently during my treatment’). In addition, participants will have the option to share any additional information about their experience of using the device through an open-ended question. Adherence to the use of the remote monitoring phone application will be assessed via three statements with participants being asked to choose the statement that best reflects their experience (‘I did not use the phone application to record my symptoms’, ‘I tried to use the phone application but gave up because it was too difficult’, ‘I occasionally used the phone application to record my symptoms throughout my treatment’ and ‘I used the phone application to record my symptoms consistently throughout my treatment’). In addition, participants will have the option to share any additional information about their experience of using the phone application through an open-ended question.

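### The plan never relates acceptance to reported use, although the Introduction motivates the frameworks by adherence; separately, the adherence questions tie stopping to difficulty

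*Protocol article*

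**What the plan says.** The Introduction describes a family of models in which use of a technology follows from the intention to use it. It presents them as a way to model both experience and adherence, and concludes that "these frameworks may be extended to modelling adherence in remote monitoring for patients with COVID-19".

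The section User acceptance of remote monitoring equipment sets out a 16-item questionnaire: "Several factors will be extracted from this model, consisting of" social influence, facilitating conditions, effort expectancy, performance expectancy and task-technology fit. It goes only to patients who report using the phone application, with or without the oximeter.

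The section Adherence to the use of remote monitoring equipment has one single-choice question for the oximeter and one for the application, each followed by an optional open-ended question. The only oximeter option for having stopped reads "I tried to use the oximeter but gave up because it was too difficult"; the application option has the same form.

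Data analysis: work package 1 gives adherence one role, in the opening descriptive step, which covers "adherence to the use of the remote monitoring equipment and acceptance towards the remote monitoring technology". After that, "structural equation modelling will be used to examine different aspects of user acceptance towards remote monitoring technology", and covariates are studied "in predicting user acceptance towards the use of remote monitoring technology".

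**The concern.** There are two separate points.

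The first concerns the analysis. Acceptance frameworks are of interest because they are meant to explain use. Here use is measured, as adherence to two devices, but it enters no stated model. The chain of modelled variables ends one step before the quantity that the Introduction gives as a reason for choosing the framework. A reader who wants to know whether patients who found the equipment easy or useful also used it more would find no answer in the planned results, although the data would be in hand.

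The second concerns the item. An option that joins a behaviour to one cause cannot be answered accurately by someone who stopped for another cause, such as feeling better or being too unwell. This affects the descriptive analysis as already planned: the count in that category would be read as patients who found the device too hard, whatever their reason.

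**Working it through.** **Role of each variable.** No power calculation or error rate in the article bears on the main point, so the check traces each measure to its place in the analysis.

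| Variable | Measured under | Role in Data analysis: work package 1 |
|---|---|---|
| Five acceptance factors | User acceptance of remote monitoring equipment | Descriptive; modelled in the SEM, or in multiple regression if the sample is too small |
| Demographics, comorbidities, prior app experience, patient–professional interaction | Their own sections | Covariates predicting acceptance |
| Behavioural intention | Not among the five factors | None stated |
| Oximeter adherence, application adherence | Adherence to the use of remote monitoring equipment | Descriptive only |

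None of the five modelled factors is intention or use, and neither adherence question is assigned to the SEM or its fallback.

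**Item counts.** The acceptance questionnaire reproduces: 2 + 3 + 4 + 4 + 3 = 16. The adherence questions do not: the text announces three statements for each device and lists four. This is clerical.

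**Response options.** For each device the four options are no use, gave up because of difficulty, occasional use and consistent use. One of the four joins behaviour to reason, and no option covers stopping for another reason. The reason given also overlaps with effort expectancy, which the article defines as ease of use. That overlap would matter only if adherence were modelled on the factors.

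**What an adherence model could detect.** The article gives a pool of 925 discharged patients and no expected response. Assumptions: 200 to 300 analysable questionnaires (200/925 = 21.6%; 300/925 = 32.4%), two-sided 5% level, 80% power, adherence treated as continuous. The approximation is r ≈ (1.96 + 0.84)/√(N − 8), where 8 is the usual 3 plus five adjusting variables:

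- N = 200: 2.80/√192 = 0.20
- N = 250: 2.80/√242 = 0.18
- N = 300: 2.80/√292 = 0.16

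These values are optimistic. A four-level item with most answers at the top carries less information than a continuous score, and application users alone span a restricted range of use.

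**The case against.** The strongest objection is that no objective is broken. Objective 1a promises to examine acceptance through factors from an integrated model; it does not promise to explain use. The Introduction's sentence on adherence is permissive. A descriptive summary of adherence plus a model of acceptance fits the objective as worded. This stands, and it limits the first point to a gap between rationale and analysis. A reader might infer that the study fails its objective; the article does not support that.

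It can also be said that the article is condensed and that structural paths may be set out in an analysis plan that is not shown. This stands in part. The article does, however, assign adherence to a step and name acceptance as what the covariates predict. Its illustrative wording about aspects of acceptance does not bring adherence in, because the preceding paragraph lists adherence and acceptance separately.

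On the item, respondents choose the closest statement, so someone who used a device until recovery could choose occasional or consistent use. The open-ended questions and the interviews can also capture other reasons. This stands as partial mitigation: the free text is optional, the interviews cover about 20 patients, and the closed categories would still be tabulated under the wrong label.

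Two further inferences should be resisted. The item wording does not cause the lack of a behavioural outcome; these are separate defects. Nor does the overlap with effort expectancy contaminate any planned analysis, since adherence is not modelled; it would arise only if a model were added with the wording unchanged.

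Finally, an adherence model would have limits of its own. Patients who report no application use receive no acceptance items, acceptance is rated after the event, and the article itself says that temporal order cannot be inferred. All of this stands and shapes the fix.

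**Conclusion.** The point holds in a limited form. The Introduction motivates the frameworks by adherence, while the stated analysis only describes adherence and stops at acceptance, so as written no acceptance factor is related to reported use. Separately, both adherence questions allow stopping only on grounds of difficulty, and the descriptive result would inherit that attribution.

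Both are inexpensive improvements, not faults that undermine the study. No rate of misclassification can be given, because the article states neither how many patients stopped nor why. The detectable correlations of 0.16 to 0.20 rest on an assumed response and a continuous-outcome approximation; they show only that the collected data could be informative, and the conclusion does not depend on them.

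**What to change.** 1. **Adherence questions.** Replace the stopping option with one that says only that the patient started and then stopped, followed by a short tick list of reasons (for example felt better, too unwell or admitted, too difficult, other). Cost: one more survey item. If the survey is already in the field, report the present category together with the free-text reasons, and add a sensitivity analysis that merges it with occasional use.

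2. **Analysis.** Add a secondary, exploratory ordinal model of application adherence, and separately of oximeter adherence, on the five factors and the covariates, within the SEM or the fallback regression. Restrict it to patients who received the acceptance items. State that application non-users are excluded by design, that the lower categories may be sparse, and that the result is a cross-sectional association. Cost: two added equations on data already planned, in a model whose sample size the authors already treat as uncertain; hence its exploratory status.

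3. **Alternative to 2.** If adherence is not to be modelled, amend the Introduction so that it no longer offers adherence as a reason for the framework, and state in the report that acceptance was not linked to use.

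4. **Clerical.** Correct three statements to four, for both devices.

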### Participants and recruitment strategy

Participants will consist of patients and healthcare staff recruited from the clinic site. First, patients who have completed their treatment via remote monitoring will be recruited to gather information on their experiences of the intervention in the form of a quantitative survey. Patient recruitment will begin in February 2021 and end in June 2021. A total of 925 patients have been discharged from the remote monitoring service. Patients will be recruited via an email sent through gatekeepers at the clinic site. All patients will receive an email with the participant information sheet and a link to an online survey. A subsample of these patients will also be recruited for a qualitative interview regarding their experiences of remote monitoring. As part of the survey, patients have the option of indicating if they wish to participate in a telephone interview and provide their contact details. Patients who consented to interview will be purposively sampled to get a representative sample based on age, gender and education. These patients will then be contacted by a member of the research team to arrange a suitable time for interview, once 7 days have passed since signing the consent form.

Second, staff who have been remotely monitoring patients with COVID-19 will be recruited via an email sent through gatekeepers at the clinic site. These participants will begin to be recruited in February 2021 and end in June 2021. A total of 25 staff worked in the virtual clinic since it was set up in April 2020. All staff who worked in the clinic will receive an invitation to participate in a qualitative interview regarding their experiences of remote monitoring from a healthcare staff perspective. If they choose to take part, a member of the research team will contact them to schedule a suitable time for a telephone interview, once 7 days have passed since signing the consent form.

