#### COVID-19 symptomatology

Patient experience of COVID-19 will be measured via a 13-item measure that assesses the presence, or absence, of COVID-19 symptoms. This measure consists of 12 commonly reported COVID-19 symptoms (fever, cough, shortness of breath or difficulty with breathing, headaches, aches and pains, fatigue/tiredness, nausea, diarrhoea, sore throat, loss of appetite, loss of taste and loss of smell) and an additional open-ended option for ‘other’. For each symptom, participants will be asked to indicate whether they experienced the symptom in the first 2 weeks following their diagnosis.

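### The latent class plan counts higher entropy as better model fit, but entropy measures how clearly patients are classified

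*Protocol article*

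**What the plan says.** Under Data analysis: work package 1, the protocol article plans a latent class analysis of acute and postacute symptoms in which "models with one to six classes will be examined". On the choice among them it says "Several fit indices will be used to determine the fit of each latent class model", and it names five: AIC, BIC, ssaBIC, entropy and the adjusted Lo-Mendell-Rubin test (LMR-A). It then gives the direction of each. For the first four: "Lower AIC, BIC and ssaBIC values and higher entropy values are indicative of better model fit". For the last: "A non-significant LMR-A value suggests that the model with one less class should be accepted".

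The classes chosen in this way become the outcome of a multinomial regression through R3STEP, described as "regressing the latent classes (identified during the class enumeration process) onto several covariates". The article nowhere describes entropy as a measure of classification certainty.

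**The concern.** The sentence puts entropy on the same footing as three penalised-likelihood criteria, as though all four answered the same question. They do not. The information criteria ask whether an extra class improves the description of the symptom data by enough to justify its parameters. Entropy asks only how close each patient's class probabilities lie to 0 or 1, given whatever model was fitted. A model with a spurious class can classify sharply, and a correct model with overlapping classes can classify poorly.

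The number of symptom profiles is the result for objective 2, and the predictor analysis is built on it. R3STEP allows for misclassification given the number of classes; it cannot repair a wrong number.

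**Working it through.** **Inputs from the article**
- Indicators (COVID-19 symptomatology): "This measure consists of 12 commonly reported COVID-19 symptoms", each present or absent, plus an open-ended item that is left out here.
- Candidate models: 1 to 6 classes.
- Sample (Participants and recruitment strategy): "A total of 925 patients have been discharged from the remote monitoring service". No response rate is given. Assumed respondents: 185 (20% of 925), 463 (50%) and 925 (100%).
- The article states no numerical figure on this point, so there is nothing to reproduce.

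**Step 1: what the indices contain**

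With K classes and 12 binary items, the number of free parameters is (K − 1) + 12K = 13K − 1, so each added class costs 13 parameters. AIC, BIC and ssaBIC all have the form −2 log L plus a penalty that grows with this count. Relative entropy is

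E = 1 − [Σᵢ Σₖ (−pᵢₖ ln pᵢₖ)] / (N ln K),

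where pᵢₖ is the posterior probability that patient i belongs to class k. It contains neither log L nor the parameter count. At K = 1 every pᵢ₁ equals 1, so the numerator is 0; the denominator is N ln 1 = 0; E is 0/0. One of the six candidate models therefore has no entropy value.

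**Step 2: entropy as the only selector**

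Simulated data: 12 binary items, 60 data sets per cell, and fits for K = 1 to 6 by EM. The assumed item probabilities were 0.9 v 0.1 (strong separation), 0.8 v 0.2 (moderate) or 0.7 v 0.3 (weak). An uneven three-class symptom profile and a one-class truth were added. Entropy chose among K = 2 to 6. Percentage of data sets with the correct K, at N = 185 / 463 / 925:

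| Assumed truth | Highest entropy | Lowest BIC, for comparison |
|---|---|---|
| 2 classes, strong | 88 / 88 / 93 | 100 / 100 / 100 |
| 2 classes, moderate | 67 / 82 / 83 | 100 / 100 / 100 |
| 2 classes, weak | 0 / 8 / 13 | 100 / 100 / 100 |
| 3 classes, strong | 38 / 52 / 60 | 100 / 100 / 100 |
| 3 classes, moderate | 0 / 13 / 28 | 100 / 100 / 100 |
| 3 classes, weak | 0 / 0 / 0 | 2 / 33 / 100 |
| 4 classes, strong | 28 / 28 / 25 | 100 / 100 / 100 |
| 4 classes, moderate | 3 / 7 / 13 | 83 / 100 / 100 |
| 4 classes, weak | 2 / 0 / 0 | 0 / 0 / 3 |
| 3 classes, uneven profile | 3 / 7 / 10 | 93 / 100 / 100 |
| 1 class | 0 / 0 / 0 | 100 / 100 / 100 |

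The Monte Carlo standard error is at most √(0.5 × 0.5 / 60) = 0.065, or 6.5 percentage points.

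The errors go both ways:
- *Too many.* Three weakly separated classes, N = 925: mean entropy rose from 0.56 at the true three classes to 0.66 at six, and entropy chose six in 47 of 60 data sets and three in none.
- *Too many.* One true class, N = 185: mean entropy still rose from 0.69 at K = 2 to 0.81 at K = 6.
- *Too few.* Four strongly separated classes, N = 925: entropy chose two in 40 of 60.

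**Step 3: entropy as one vote among several**

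This is nearer to the plan. Three true classes (35/40/25%) were simulated with two assumed profile sets. The vote was a plurality of AIC, BIC and ssaBIC, with or without entropy; ties went to BIC, else to the smallest K. LMR-A was not simulated.

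| Profiles | N | Chosen K changed by entropy | Correct without → with entropy |
|---|---|---|---|
| Distinct | 200 | 12% | 59% → 65% |
| Distinct | 300 | 3% | 90% → 89% |
| Distinct | 450 | 3% | 100% → 97% |
| Severity-ordered | 200 | 15% | 50% → 42% |
| Severity-ordered | 300 | 26% | 61% → 40% |
| Severity-ordered | 450 | 11% | 80% → 70% |

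The largest loss is 61 − 40 = 21 percentage points. The share choosing more than three classes moved by only −6 to +5 points.

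A separate run of the same kind, with other assumed profiles (N = 200 and 450, 60 data sets in each of four cells), had K changed by entropy in 0–23% of data sets. Correct choices out of 60 went 40 → 34, 19 → 18, 17 → 6 and 60 → 60.

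**The case against.** The strongest reply is that entropy is one of five indices and that the plan never lets it decide alone. This stands, and it limits the size of the point. LMR-A is also the only index that comes with an accept-or-reject instruction, and that instruction works against extracting too many classes. It was not simulated, so the true influence of entropy under the full set of five is unknown.

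It does not follow that the clause is harmless. In a further run (three true classes, N = 200, 300 and 450, 80 data sets per cell), the number favoured by entropy differed from that favoured by BIC in 71–99% of data sets. Entropy would therefore often enter as contrary evidence about fit, which it is not.

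A reader might infer four stronger claims that are not supported:
- *Entropy almost never finds the right number.* It did so in 67–93% of data sets with two strongly or moderately separated classes and in 25–60% with three or four strongly separated ones. The article says nothing about separation. Two different assumed sets of distinct three-class profiles gave 2–3% and 19–24%.
- *The plan will produce spurious small classes.* The votes in step 3 do not show this; errors went in both directions.
- *BIC should take the lead and AIC should be demoted.* With severity-ordered profiles BIC chose two classes instead of three in 83–98% of data sets in one simulation and in all 120 in another, while AIC was right in 42–48% in the first.
- *The lack of an order of priority, of a bootstrap likelihood ratio test or of a minimum class size is an error.* These are details or preferences that a condensed article may leave to a fuller plan.

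**Conclusion.** The statement that higher entropy indicates better fit is incorrect as written. That conclusion rests on the definition of entropy, including its absence at K = 1, and needs no simulation.

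The size does rest on assumptions: class profiles, class shares and response rates that the article does not give, and fewer random starts than planned (20 starts with 4 final optimisations in step 2, where the plan says "500 random sets of starting values will be used followed by 100 final stage optimisations"). Under those assumptions, the realistic effect is the one in step 3: the chosen number changes in roughly 0–26% of data sets, with accuracy mostly unchanged or lower and the clearest loss where profiles differ by severity. The wider 0–93% range describes entropy alone, which is not the plan's rule.

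Severity is minor to moderate. Entropy is one index of five, but the class count is the result for objective 2 and fixes the outcome of the R3STEP regression.

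**What to change.** In Data analysis: work package 1, delete the entropy clause from the sentence on the direction of the indices, and take entropy off the list of indices used to choose the number of classes. Choose on the information criteria and LMR-A already named. Then add a sentence such as: *Entropy will be reported for the selected model as a measure of how clearly patients are assigned to classes, and will not be used to select the number of classes.*

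The cost is one sentence of text. No new data and no additional analysis are needed.
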